## Abstract

**Introduction:**

Vitiligo is a condition resulting in white patches on the skin. People with vitiligo can suffer from low self-esteem, psychological disturbance and diminished quality of life. Vitiligo is often poorly managed, partly due to lack of high-quality evidence to inform clinical care. We describe here a large, independent, randomised controlled trial (RCT) assessing the comparative effectiveness of potent topical corticosteroid, home-based hand-held narrowband ultraviolet B-light (NB-UVB) or combination of the two, for the management of vitiligo.

**Methods and analysis:**

The HI-Light Vitiligo Trial is a multicentre, three-arm, parallel group, pragmatic, placebo-controlled RCT. 516 adults and children with actively spreading, but limited, vitiligo are randomised (1:1:1) to one of three groups: mometasone furoate 0.1% ointment plus dummy NB-UVB light, vehicle ointment plus NB-UVB light or mometasone furoate 0.1% ointment plus NB-UVB light. Treatment of up to three patches of vitiligo is continued for up to 9 months with clinic visits at baseline, 3, 6 and 9 months and four post-treatment questionnaires.

The HI-Light Vitiligo Trial assesses outcomes included in the vitiligo core outcome set and places emphasis on participants’ views of treatment success. The primary outcome is proportion of participants achieving treatment success (patient-rated Vitiligo Noticeability Scale) for a target patch of vitiligo at 9 months with further independent blinded assessment using digital images of the target lesion before and after treatment. Secondary outcomes include time to onset of treatment response, treatment success by body region, percentage repigmentation, quality of life, time-burden of treatment, maintenance of response, safety and within-trial cost-effectiveness.

**Ethics and dissemination:**

Approvals were granted by East Midlands—Derby Research Ethics Committee (14/EM/1173) and the MHRA (EudraCT 2014-003473-42). The trial was registered 8 January 2015 ISRCTN (17160087). Results will be published in full as open access in the NIHR Journal library and elsewhere.

**Trial registration number:**

ISRCTN17160087.

Strengths and limitations of this studyAnswers research questions prioritised by people with vitiligo and healthcare professionals as a part of a James Lind Alliance Priority Setting Partnership.Appropriately powered, pragmatic, randomised controlled trial, which may influence clinical decision making for a condition with little high-quality evidence to support treatment options.Trial places emphasis on patient-reported outcomes and includes the core outcome set for vitiligo.Blinding of treatment allocation may be compromised due to observable side effects (eg, erythema and tanning of the surrounding skin), particularly for those receiving active light therapy.Primary outcome is based on participant-reported treatment success at 9 months (Vitiligo Noticeability Scale), further improvement may occur after this time as residual hyperpigmentation resolves.

## Introduction

Vitiligo is a chronic progressive condition causing loss of skin pigmentation. It affects around 0.5%–1% of the world’s population, and can develop at any age, although onset between the age of 10 and 30 years is most common.^1–4^ Vitiligo can have a major impact on the quality of life of affected people,^5^ who often experience psychological problems such as shame, depression and anxiety, low self-esteem and social isolation.^6 7^

Current clinical guidelines for the management of vitiligo recommend narrowband ultraviolet-B light (NB-UVB), topical corticosteroids, topical tacrolimus and combination therapies.^8 9^ However, the evidence base for treatments is currently limited.^10 11^

A Cochrane systematic review assessing interventions for vitiligo was updated in 2015.^12^ This review identified 96 randomised controlled trials (RCTs) of vitiligo treatments, involving 4512 participants. Despite this large number of trials, the quality of the included studies was generally poor, making it difficult to make firm recommendations for vitiligo treatment. The majority of the studies included fewer than 50 participants, were at high or unclear risk of bias and few involved children. Nevertheless, the Cochrane review identified some evidence in support of NB-UVB, and the combination of NB-UVB with other active interventions (eg, topical corticosteroids or calcineurin inhibitors) appeared to be more effective than monotherapy. A 2016 review of the use of NB-UVB for the treatment of vitiligo^13^ also concluded that guidance on dosing and administration of NB-UVB requires further study.

There is some evidence to suggest that starting vitiligo treatment when lesions first appear is likely to result in better treatment response, when vitiligo patches are actively changing and some melanin is still present.^14^ However, current practice is to reserve NB-UVB treatment for patients with widespread and established vitiligo,^8^ as the treatment requires thrice weekly visits to the hospital for full body light therapy. The recent availability of hand-held NB-UVB units for private purchase on the open market means that early intervention using treatment at home is now a possibility. Benefits of home-based treatment, if shown to be safe and effective, would be a reduction in time and financial burden for patients and hospital services, and reduced exposure of healthy skin to NB-UVB light as treatment can be targeted more effectively. Our small pilot RCT, involving 29 participants, compared hand-held NB-UVB with dummy devices for the management of vitiligo.^15^ This pilot demonstrated that people with vitiligo were keen to use home-based light therapy, and that the devices were safe and well tolerated when used in a domestic setting.

A James Lind Alliance Priority Setting Partnership identified a ‘top 10’ list of priority areas for vitiligo research that are important to people with vitiligo and healthcare professionals responsible for their care.^16^ Two of these prioritised areas relate to the use of light therapy for the management of vitiligo: ‘Which treatment is more effective for vitiligo: steroid creams/ointments or light therapy?’ and ‘How effective is UVB therapy when combined with creams or ointments in treating vitiligo?’ The prioritisation work was shared with the NIHR Health Technology Assessment Programme who subsequently invited applications to address these two priority topics in open competition. The contract to conduct the commissioning brief was awarded to this team.

### Objectives

Primary objective:To evaluate the comparative safety and effectiveness of home-based interventions (potent topical corticosteroids and hand-held NB-UVB light) for the management of early and limited vitiligo in adults and children. Specifically, we are comparing:Potent topical corticosteroid (mometasone furoate 0.1% ointment) with hand-held NB-UVB light;Potent topical corticosteroid (mometasone furoate 0.1% ointment) with combination of hand-held NB-UVB light and potent topical corticosteroid.

Secondary objectives:To assess whether treatment response (if any) is maintained once the intervention is stopped.To compare the cost-effectiveness of the interventions from a National Health Service (NHS) and a family perspective.

## Methods

The analysis and reporting of the trial will be in accordance with Consolidated Standards of Reporting Trials guidelines.^17^

### Study design and setting

The trial is a multicentre three-arm, parallel group, pragmatic, placebo-controlled RCT, recruiting adults and children with early and limited vitiligo. The trial treatments are home-based therapies (potent topical corticosteroid and hand-held NB-UVB), and their use is prescribed and overseen in a secondary care setting across 18 hospitals in the UK. A full list of recruiting centres can be found in the ’Acknowledgements' section. A mixed-methods process evaluation is being conducted alongside the HI-Light Vitiligo Trial. The full protocol is available at www.vitiligostudy.org.uk.

### Participants

#### Eligibility

##### Inclusion criteria

Participants aged 5 years and over with a diagnosis of non-segmental vitiligo, limited to approximately 10% or less of body surface area, and at least one vitiligo patch that has been active in the last 12 months (reported by the participant, or parent). Participants should be willing to stop any other active therapies for their vitiligo at time of randomisation, be able to administer the trial treatments safely at home (able to follow the treatment instructions and children able to comply with the necessary safety precautions). Participants also need to be willing and able to give informed consent (or parental/guardian consent in the case of children).

##### Exclusion criteria

Potential participants with segmental or universal vitiligo, vitiligo limited to areas contraindicated for treatment with potent topical corticosteroid (eg, around the genitals) or evidence of marked Koebner phenomenon (lesions appearing in sites of skin trauma) as such potential participants are likely to require urgent care. Also excluded are potential participants with a history of skin cancer, radiotherapy use or photosensitivity; women who are pregnant, breastfeeding or likely to become pregnant during the 9-month treatment period; those currently using immunosuppressive drugs, or involved in another clinical trial and those with allergy or contraindication to mometasone furoate or any of its excipients. Potential participants are not randomised into the trial if the research nurse or investigator feels that they are unable to follow the treatment instructions, or if children are unable to comply with the necessary safety precautions.

#### Participant timeline

Participants are enrolled in the trial for a total of up to 21 months (9 months treatment phase, up to 12 months follow-up). During the treatment phase, participants attend a hospital clinic five times (two consecutive days at baseline for recruitment, medical photography, photosensitivity assessment (minimum erythema dose (MED) test) and training in use of the interventions), followed by assessment at 3, 6 and 9 months for compliance and outcome. The additional follow-up is by 3-monthly questionnaires, self-completed by post or email link. Due to trial timelines, participants recruited towards the end of the recruitment may be followed-up for a shorter period of time.

Flow of participants through the trial is summarised in figure 1, and details of the data collection schedule are summarised in table 1.

**Figure 1 F1:**
[figure not shown]
Flow of participants through the trial. MED, minimum erythema dose.

**Table 1 T1:** Timetable of study assessments

Outcome collected	Prescreen	Visit 1 screening	Visit 2 baseline	Telephone screen (2 weeks)	Visit 3 (3 months)	Visit 4 (6 months)	Visit 5 (9 months)	Questionnaires (12, 15, 18 months)	Questionnaire (21 months)
Eligibility checks	✓	✓	✓						
Consent		✓							
Minimum erythema dose (MED) test		✓							
Baseline characteristics (alternative timing)		✓	(✓)						
Digital images (alternative timing)		✓	(✓)				✓		
Training session (alternative timing)		✓	(✓)						
Supervised treatment session		✓	(✓)						
MED test results			✓						
Randomisation			✓						
Telephone support check				✓					
Vitiligo Noticeability Scale					✓	✓	✓	✓	✓
% repigmentation					✓	✓	✓		
Onset of treatment response					✓	✓	✓		
Maintenance of treatment response								✓	✓
Quality of life questionnaires		✓					✓		✓
Adverse reactions				✓	✓ and Diary	✓ and Diary	✓ and Diary		
Treatment usage and adherence				✓	✓ and Diary	✓ and Diary	✓ and Diary		
Health resource use		✓			✓ and Diary	✓ and Diary	✓ and Diary	✓	✓

#### Recruitment

Potential participants are identified through secondary care dermatology and paediatric clinics, through mailshots from general practices and by self-referral as a result of community advertising and trial publicity. Potential participants are initially screened by telephone in order to ensure that only people who are potentially eligible to take part are invited to attend a clinic appointment.

### Randomisation and blinding

Participants are randomised to one of three treatment groups in a ratio of 1:1:1 as follows:Topical corticosteroid ointment plus dummy NB-UVB light (corticosteroid only);Vehicle ointment plus NB-UVB light (light therapy only);Topical corticosteroid ointment plus NB-UVB light (combination therapy).

Randomised allocation to treatment groups is minimised by recruiting centre, body region of target patch (face and neck, hands and feet or rest of the body) and age (5–16 years or >16 years), weighted towards minimising the imbalance in trial arms with a probability of 0.8. After all eligibility criteria have been confirmed and medical photographs taken, participants are randomised by staff at the recruiting hospital via a secure web server created and maintained by the Nottingham Clinical Trials Unit.

Participants are only randomised into the trial once they have completed the training in use of the trial interventions, the results of the MED test are known and the participant has attended medical photography for their baseline digital photograph.

Participants, research nurses, principal investigators, members of trial management group and data analysts are blinded to treatment allocation. Only the Nottingham Clinical Trials Unit (NCTU) programmer, the medical physics staff, pharmacy staff and the NCTU Quality Assurance staff have access to the treatment allocation schedule for the sole use of preparing, blinding and checking of the trial treatments.

While every effort is made to maintain blinding of the trial interventions, there is a risk that participants may be able to guess their treatment allocation as a result of side effects of the interventions (eg, redness and tanning of the skin). To minimise detection bias, outcomes will be assessed by blinded assessors (both independent clinicians and a panel of patients), using digital images taken at baseline and at 9 months. Participant information leaflets will emphasise that all participants will receive at least one active treatment for their vitiligo, thus reducing potential unblinding due to lack of treatment response. During our previous trial in which participants were randomised to active or dummy light therapy devices, 70% (19/27) of participants and 40% (16/27) of research nurses, guessed treatment allocation correctly. The main reasons for unblinding of the research nurses were redness of the skin (30% (3/10)) and improvement in vitiligo (60% (6/10)) in the active group, and lack of treatment response (100% (6/6)) in the placebo group.

### Interventions

#### Topical therapy: potent topical corticosteroid

Mometasone furoate 0.1% ointment (Elocon, Merck, Sharp and Dohme, PL00025/0578), a potent corticosteroid used once daily, has been recommended in the European Clinical Guidelines for the management of vitiligo.^9^ In order to minimise the risk of adverse reactions, the Guidelines recommend a discontinuous regimen involving periods of use followed by break periods. Possible adverse reactions to mometasone furoate 0.1% (as listed in the Summary of Product Characteristics^18^) include: infection, folliculitis, paraesthesia, burning sensation, contact dermatitis, skin hypopigmentation, hypertrichosis, skin striae, acneiform dermatitis, skin atrophy, pruritus, application site pain and visual disturbance. Participants are advised to stop treatment with the ointment if they notice any side effects and to contact the local research team for review and advice on when to restart treatment.

#### Topical therapy: vehicle ointment

The vehicle ointment is an inert ointment (white soft paraffin) present in the base of mometasone furoate ointment. It is relatively free of side effects.^19^

#### Topical therapy: treatment regimen

To minimise the risk of adverse reactions, topical therapy is to be applied as a thin layer to the affected patches once daily on alternate weeks (1 week on, 1 week off), for a period of 9 months. Participants are instructed that topical therapy should be applied at least 2 hours after the hand-held light device is used in order to avoid interaction of the NB-UVB light and topical corticosteroid.

Participants are initially supplied with two x 90 g tubes of ointment after randomisation. Additional tubes are prescribed by the investigator as required.

#### Light therapy: NB-UVB device

Several brands of hand-held NB-UVB units are CE marked for use in treating vitiligo and suitable for use at home. Dermfix 1000 MX units are being used for this trial.

Known adverse reactions to NB-UVB light include: erythema, blistering, burns, pruritus, perilesional hyperpigmentation, hypersensitivity reactions, cold sores and dry skin. Potential long-term risks include skin ageing and increased risk of skin cancer. Side effects can be reduced by appropriate use of the device.

#### Light therapy: dummy device

The dummy light therapy device is identical to the active device, with the exception that a specially designed spacer comb, identical to that found on the active device, is used to block the transmission of NB-UVB light to the skin. Active and dummy devices are tracked using manufacturer’s serial numbers. Experience from our pilot trial^15^ has shown that the use of a dummy device is acceptable to patients and is effective in blocking the UVB radiation.

There are no known side effects of the dummy NB-UVB devices.

#### Light therapy: quality control prior to distribution

All light therapy devices are tested for safety and output by the Medical Physics Department at Nottingham University Hospital NHS Trust before sending to participants. If an active device is found to have an output that is ±10% of the expected mean output, or if a dummy device tests positive for any NB-UVB emission, the device is returned to the manufacturer. Any device which is damaged or ceases to function during the treatment phase is replaced with a new unit.

#### Light therapy: regimen

Although NB-UVB (UV radiation wavelengths of 311–312 nanometres) is now the most common form of light therapy used to treat skin conditions, many gaps remain in knowledge about its use. In a 2016 paper,^13^ Madigan *et al* published a list of 12 key questions regarding the use of narrowband UVB for generalised vitiligo. How each of these questions has been addressed within the context of the HI-Light trial is presented in table 2. Prior to randomisation, all participants receive an MED test, to ensure eligibility for the trial. Results of the MED test are not used to determine starting dose of the light therapy, but instead to ensure that the participant does not have any undiagnosed photosensitivity disorder. All participants follow a predefined treatment schedule for the light treatment, with a starting dose of 0.05 J/cm^2^ (see supplementary appendix 1).

10.1136/bmjopen-2017-018649.supp1Supplementary file 1

**Table 2 T2:** Key questions regarding the use of NB-UVB for generalised vitiligo^13^

Question		Strategy tested in the HI-Light Vitiligo Trial
1	What is the optimal weekly frequency of NB-UVB treatment?	HI-Light Trial: every other day (3–4 times weekly). Rationale: this is the most commonly used treatment regimen in the UK.
2	With regard to initial dosing, which strategy should ideally be employed?	HI-Light Trial: all participants started on the same low dose, 0.05 J/cm^2^. Rationale: MED test was carried out before treatment, but only to identify any undiagnosed cases of photosensitivity. Starting at a fixed low dose to minimise the risk of symptomatic erythema was felt to be safer for home delivery of NB-UVB.
3	At subsequent treatments, what increments should be used for dose escalation in the absence of perceptible erythema?	HI-Light Trial: 10% dosing increase after each treatment not followed by erythema. Rationale: this reflects typical clinical practice in UK phototherapy services
4	What is the maximum acceptable dose to be given in a single treatment?	HI-Light Trial: maximum dose in the trial is 2.81 J/cm^2^. Rationale: this reflects typical clinical practice in UK phototherapy services.
5	What is the ideal practice for dose adjustment following symptomatic erythema?	HI-Light Trial: patient self-adjustment for grades 1 and 2 erythema (according to flow chart in patient handbook) and investigator adjusted dosing for grades 3 and 4. Rationale: the upwards and downwards dosing used in the trial reflects the clinical practice of most UK phototherapy services.
6	How should the protocol be adjusted for missed doses?	HI-Light Trial: varies in function of number of missed treatments. 1 or 2 missed: go back one step on treatment schedule; 3 missed: go back two steps on treatment schedule; 4–6 missed: 50% of last dose; 6+ missed restart treatment schedule from beginning. Rationale: this conservative approach ensures that participants who have missed a lot of doses are not at risk of symptomatic erythema when they restart treatment.
7	How should a ‘course’ of NB-UVB therapy be defined? (ie, At what interval should further exposure be reassessed?)	*Not directly applicable within the scope of the trial.*
8	What is the maximum number of exposures allowable for patients with vitiligo given the potential risk of carcinogenesis with NB-UVB?	*Not directly applicable within the scope of the trial.* Participants in the trial will only be treating limited areas of skin and the total number of treatments will be less than the current maximum recommended number of treatments.
9	Should dosing strategies differ when treating children with vitiligo?	HI-Light Trial: children are treated in the same way as adults. Parents are given the choice of what patches they are comfortable treating, and may opt out of treating sensitive areas if they wish to do so. Rationale: the home-based treatment is more flexible than hospital-based full-body treatment, so it is possible for children to be treated in the same way as adults.
10	Should shielding of sensitive structures (eyelids, areolas and genitals) be a universal requirement, or is it safe to expose these areas if affected by vitiligo?	HI-Light Trial: the trial excludes treatment of vitiligo in the genital region. Other sensitive areas can be treated if they are affected by vitiligo, but will not otherwise be exposed to NB-UVB due to the localised nature of treatment using a hand-held device. If treating the eyes, patients are advised to seek assistance from someone else so that they can keep their eyes closed during treatment, thus reducing the risk of accidental exposure during treatment.
11	What is the most accurate definition of treatment unresponsiveness?	HI-Light Trial: treatment response is assessed in terms of its onset; unresponsiveness would be defined by patient report of ’stayed the same' or ’got worse' in response to the question, ‘Compared with the start of the study, has there been a change in the vitiligo patch?' Participants are encouraged to continue treatment for as long as they are happy to do so. The trial may provide useful data on when and how to define treatment unresponsiveness.
12	How frequently should patients with vitiligo undergo surveillance following completion of a NB-UVB treatment protocol for both signs of relapse and adverse events? Is there a role for phototherapy in maintenance following repigmentation?	HI-Light Trial: long-term treatment response is being assessed 3-monthly for 1 year following completion of NB-UVB treatment. The trial has not been designed to evaluate the use of intermittent treatment for maintenance of response. Rationale: patients are particularly interested in how long treatment response might last and this is now a core outcome domain for vitiligo clinical trials.

MED, minimum erythema dose; NB-UVB, narrowband ultraviolet B-light

Treatment is self-administered at home, every other day, for a period of 9 months. If the vitiligo is on the face, or in an area that is inaccessible, participants are advised to seek help from someone else to administer the treatment. Parents/guardians are instructed in how to administer the treatment for their child.

The exposure time for each session is increased incrementally. Participants are asked to keep a record of their treatments in a treatment diary. Details are provided to participants on how to progress through the treatment schedule, step down or temporarily stop, depending on treatment response (a summary of instructions can be found in online supplementary appendix 2). Full instructions from the participants’ handbook can be found at www.vitiligostudy.org.uk. All devices are supplied with gloves and UV protective goggles (for both the participants and their helper as required), which must be worn at all times during use.

10.1136/bmjopen-2017-018649.supp2Supplementary file 2

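### Table 2 of the protocol article gives two different restart instructions for exactly six missed light treatments, and nothing else in the article says which applies

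*Protocol article*

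**What the plan says.** In the protocol article, section Light therapy: regimen, Table 2 sets out how the trial deals with a published list of questions on narrowband UVB. Question 6 covers missed doses and has four bands. The first two are "1 or 2 missed: go back one step on treatment schedule; 3 missed: go back two steps on treatment schedule". The third and fourth are "4–6 missed: 50% of last dose; 6+ missed restart treatment schedule from beginning". The rationale in the same cell calls the approach conservative and says it is meant to keep people who have missed many doses from symptomatic erythema when they resume.

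Other entries fix the doses involved. Question 2 gives the starting dose: "all participants started on the same low dose, 0.05 J/cm^2". Question 3 gives the escalation: "10% dosing increase after each treatment not followed by erythema". Question 4 gives the ceiling: "maximum dose in the trial is 2.81 J/cm^2". The text below the table adds: "Treatment is self-administered at home, every other day, for a period of 9 months". For the instructions that participants receive, the article points to supplementary appendix 2 and to the participants' handbook on the trial website.

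**The concern.** Six is the top of the third band, and a plus sign after a number ordinarily means that number or more, so six also opens the fourth band. One band halves the last dose and the other sends the participant back to the first step of the schedule. For most last doses these are different doses.

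If the same wording reached users, the dose after six missed sessions would depend on which line was read. That bears on erythema risk in one direction and on cumulative exposure in the other. The rule has a stated safety purpose, and at this count the table does not say what to do. Table 2 is also the article's own record of the strategy tested, so anyone reporting or reproducing the regimen would inherit the ambiguity.

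**Working it through.** **Do the bands overlap?** Mapping each count to the bands in Table 2, question 6:

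| Sessions missed | Instruction(s) that apply |
|---|---|
| 1, 2 | back one step |
| 3 | back two steps |
| 4, 5 | half the last dose |
| 6 | half the last dose, and also restart |
| 7 or more | restart |

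Only six maps to two instructions.

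**How far apart are the two doses at six?** Let L be the last dose. Halving gives 0.5 × L. A restart gives 0.05 J/cm² (question 2). The ratio is 0.5 × L / 0.05 = 10 × L, with L in J/cm² and at most 2.81 (question 4).

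| Last dose L (J/cm²) | Half of L | Restart dose | Ratio |
|---|---|---|---|
| 0.05 | 0.025 | 0.05 | 0.5 |
| 0.10 | 0.05 | 0.05 | 1 |
| 0.50 | 0.25 | 0.05 | 5 |
| 1.00 | 0.50 | 0.05 | 10 |
| 2.00 | 1.00 | 0.05 | 20 |
| 2.81 | 1.405 | 0.05 | 28.1 |

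The gap is nil at 0.10 J/cm². Below that, half the last dose is less than the starting dose. The 28-fold figure is the upper bound.

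**Can the upper doses be reached?** With 10% steps from 0.05 J/cm², the number of steps to the maximum is ln(2.81/0.05)/ln(1.1) = 42.3. Nine months of alternate-day treatment gives about 9 × 30.44 / 2 = 137 sessions. The maximum is therefore attainable if escalation is not held back much by erythema or missed sessions.

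**What does a restart cost in time?** From 0.05 back to 1.405 J/cm² takes ln(1.405/0.05)/ln(1.1) = 35.0 steps. At one step every two days that is about 70 days, or 70/274 = 26% of a nine-month (9 × 30.44 = 274 day) treatment phase.

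**Is a count of six plausible?** Six missed alternate-day sessions cover about 6 × 2 = 12 days, which a holiday or a short illness could produce. The article gives no figure for how often exactly six are missed, so no frequency can be put on it.

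**Which arms are affected?** Under Randomisation and blinding, two of the three arms use active devices. In the corticosteroid-only arm the dummy device blocks UVB, so following either instruction changes no delivered dose.

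**The case against.** Four arguments on the other side deserve weight.

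- **Table 2 is a summary.** The working instructions are in appendix 2 and the handbook, and participants also have face-to-face training, written instructions, a two-week call and three-monthly clinic checks. A reader might infer that home users were given contradictory instructions. The article does not show that. It also does not say who applies the missed-dose rule: question 5 explicitly gives self-adjustment for mild erythema to the patient, while question 6 is silent. This argument stands and limits the point to the article's table.
- **The plus sign may have been loose shorthand for more than six.** That would make the list coherent, and the lower bands do not overlap. But the text does not say so, so the table still needs correcting.
- **The 28-fold figure mostly measures the step built into the rule.** Under any wording, a participant at the maximum moves from 1.405 to 0.05 J/cm² when one more missed session crosses the cut-off. The overlap leaves open only whether that step falls between five and six or between six and seven. Neither reading at six produces a dose that the rule does not already prescribe at five or seven. This stands, so 28-fold should not be read as the typical size of the problem.
- **The statistical plan is untouched.** The primary comparison is by allocated group regardless of adherence. This stands too.

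**Conclusion.** The contradiction is real, and it is confined to one count in one table. For exactly six missed sessions, Table 2 gives two instructions, and nothing else in the article chooses between them. The ratio of the two resulting doses is ten times the last dose in J/cm², up to 28.1 at the maximum, and it matters for delivered UVB only with active devices.

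This rests on the ordinary meaning of a plus sign, on the starting and maximum doses in Table 2, and on the article alone. If appendix 2 and the handbook are clear, only the article's wording is at fault. If they carry the same overlap, the matter becomes one of participant instruction and is more pressing. A reader might go further and infer a threat to the trial's result. The article does not support that: the overlap does not enter the sample size, the error rates or the primary analysis. It is a minor to moderate wording contradiction in a dosing rule.

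**What to change.** Reconcile the third and fourth bands in Table 2, question 6, so that every count of missed treatments maps to exactly one instruction. Check that the table, supplementary appendix 2 and the participants' handbook then agree. If the overlap is also in the participant materials, send sites a short note stating which instruction was intended. The clinical team decides which instruction applies at six; this review takes no view on it.

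The cost is a wording correction in one table cell and a comparison of three documents, plus a corrected handbook page and a site note if the check finds the same overlap. No analysis needs to change.
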